### Concealment mechanism {16b}

The schools will be immediately informed about the allocation via mail. For randomisation, we will use Microsoft Excel. To proceed with organising the appointments and the intervention, schools have to know to which group they have been allocated. The allocation will be executed in the presence of a third independent employee of the clinic (SM).

### Implementation {16c}

As there are no patients involved in this study, we do not expect a risk of bias associated with the methods of sequence generation and/or inadequate allocation concealment. Schools do have to know in which group they are in, in order to proceed with the organisation of appointments and intervention.

## Assignment of interventions: blinding

### Who will be blinded {17a}

Due to the study design and the planned intervention, there will be no blinding. Schools need to know the group to which they have been allocated in order to plan and organise the next steps within the study. We do not expect any ascertainment bias shown in the answers to the questionnaires between the two groups.

### Procedure for unblinding if needed {17b}

Not applicable. Due to the study design, schools and participants will know the group to which they have been assigned. However, to avoid manipulation of the questionnaires, participants will be unaware of the study hypotheses. The WL control group will merely be told that the intervention will take place in 6 months and that data will be collected in the interim.

## Data collection and management

### Plans for assessment and collection of outcomes {18a}

#### Data collection

The baseline data collection is scheduled for autumn 2022, if permission and recruitment are completed in time. The intervention should begin immediately after baseline data collection. During this time, the usual curriculum will be run in the waiting list control group. The post-data assessment will take place within 7 days post-intervention. The first follow-up will take place 3 months post-intervention (spring 2023) and the second follow-up will take place 6 months post-intervention (summer 2023). If permission and recruitment take longer than expected, e.g. due to possible pandemic-related restrictions, we plan to extend the recruitment phase until spring 2023.

#### Measures- questionnaire

Data collection will be conducted anonymously through a self-administered questionnaire completed on participants’ own mobile devices either in school or at home. If no mobile device is available at school, students will either receive a loan device or will be able to use the school’s IT room. Each student will generate an individual 12-item code consisting of numbers and letters based on different questions. This code can be used to link data from the three measurement time points without the need for a list combining name and data set, meaning that data security is guaranteed at all times. We have chosen to use mobile devices for the following reasons: (1) careful use of environmental resources, (2) greater willingness and enthusiasm to fill out the questionnaires on the part of the students, and (3) fewer missing data. A list of all questionnaires is presented in Table 1. Each questionnaire has been selected carefully (validated among the target group, sufficient to good psychometric properties, aimed at assessing a targeted construct, no iatrogenic effects known so far, use of an adapted version for adolescents whenever possible).

For the assessment of our primary outcome stress, we will use the 10-item version of the *Perceived Stress Scale* (PSS-10; original by Cohen, Kamarck, and Mermelstein [67], German validation by Klein, Brähler et al. [47]; *α* = .84). The PSS-10 examines the degree to which life seems unpredictable, uncontrollable, and overwhelming, with responses referring to the last month. PSS-10 has been found to correlate positively with depression and anxiety negatively ones to QoL.

Emotion regulation will be assessed using the *Difficulties in Emotion Regulation Scale* DERS-SF [48], an 18-item short version of the original 36-item version [73, 74]. The DERS-SF measures emotion regulation on six dimensions and has shown a Cronbach’s *α* of .90.

To assess self-compassion, we will use the total summed score of the short form of the *Self-Compassion Scale* (SCS-SF) [49]; the original *Self-Compassion Scale* (SCS) was developed by [75, 76]. The original English-language 12-item short form has shown adequate internal consistency (Cronbach’s *α* > .86) and a near-perfect correlation with the long-form SCS. Within a German sample and for the German validation, the SCS also showed good internal consistency for the subscales, ranging from .71 to .79 [76].

The *Insomnia Severity Index* [69] was developed by Morin [77] and the German validation was conducted by Gerber [53]. It is a useful screening instrument consisting of seven items, including night-time and daytime components of insomnia. A Cronbach’s *α* of .76 has been reported for boys and girls.

The four-item Patient Health Questionnaire (PHQ-4) is a brief screening scale for symptoms of depression and anxiety, showing good internal consistency (Cronbach's α > 0.80) [51, 78]. The PHQ-4 is a combination of the 2-item Patient Health Questionnaire (PHQ-2) [79, 80] and the 2-item Generalized Anxiety Disorder screening tool (GAD-2) [81]. Questions are answered on a scale ranging from 0 to 3 and result into mild (3-5), moderate (6-8), and severe PHQ-4 categories (9-12).

The *Short Evaluation of Eating Disorders* (SEED) [54] consists of six items exploring the main symptoms of anorexia nervosa (underweight, fear of gaining weight, body image disturbance) and bulimia nervosa (binge eating, compensatory behaviour, preoccupation with body shape and weight) within the last month or week. The SEED has previously been employed successfully in school students [82].

The five-item *World Health Organization Well-Being Index* (WHO-5) was first published in 1998 and has been translated into more than 30 languages. It measures subjective well-being and was derived from the WHO-10 [83], which was itself derived from a 28-item version [84]. It is used worldwide, and a recent systematic review found the WHO-5 to be highly clinimetrically valid, sensitive, and specific [85].

To assess the students’ self-esteem, the *Single-Item Self-Esteem Scale* (SISE) will be used [86], which has its origin in the Rosenberg Self-Esteem Scale [68] and has been shown to be a valid, reliable, economical, and practical instrument in German samples [56].

To evaluate participants’ ability to cope with internal or external stressors, we will assess their resilience, using the *Connor-Davidson Resilience Scale-short form* (CD-RISC 10), which is derived from the long version designed by Connor and Davidson in 2003 [87]. The CD-RISC is widely used and has good psychometric properties (*a* = .84) [57].

To assess protective factors for mental health in children and adolescents, we will use the German Scales for the Assessment of Protective factors (*Skalen zur Erfassung von Schutzfaktoren*) following the suggestions of Bettge and Ravens-Sieberer [55]. The scales have been validated in adolescents aged from 11 to 17 years and proved to be valid and practicable.

To measure non-suicidal self-injury (NSSI), we will use a shortened version of the nine-item *Deliberate Self-Harm Inventory* (DSHI-9), which was used in the SEYLE study. The original version of the DSHI [88] contains 17 items, and the DSHI-9 is an adaptation for adolescents [89]. To avoid confusing adolescents who do not harm themselves, we will introduce the questionnaire with a single question (“Have you ever hurt yourself with the intention of causing yourself physical pain?”). If they answer with “Yes”, NSSI will be explored further in terms of frequency, severity, and duration, using the DSHI-9. If they answer with “No”, NSSI will proceed to the next questionnaire. The internal consistency for the DSHI-9 lies between alpha = .66 and .85 [90].

In addition to demographic questions, the socioeconomic status will be captured using the *Family Affluence Sale* (FAS; [58] and the MacArthur Scale [91].

Finally, six questions regarding the COVID-19 pandemic will be asked, which explore stress factors, general mood, and well-being in families during the pandemic. These questions are from the Corona Health App, which was developed as part of a scientific cooperation between university partners, the Robert Koch Institute, and software companies (for detailed information, see www.corona-health.net).

### Plans to promote participant retention and complete follow-up {18b}

To promote retention throughout the study and maximise the completeness of data collection, we will give monthly feedback to the school heads, the involved teachers, and the participating students. Feedback may consist of a little insight into results of the first data collection, schedule reminders, a newsletter, or small business gifts (pens or stickers).

Should any student withdraw from the study for any reason, he or she must inform us, whether we are permitted to use the data already collected or we should delete it. If deletion is requested, the student must provide us with his/her pseudonym to enable deletion.

If non-retention occurs and more than one follow-up data assessment is missing for a student, this student will not be included in the analysis.

### Data management {19}

#### Data entry

Within the study *LessStress,* all data will be entered electronically. This will usually be accomplished using the participants’ own devices (cell phones, tablets, laptops) or they can use devices provided by their school. The data collection itself will take place online using the SoSciSurvey. This software solution is firmly established in academic research, e.g. at the University of Würzburg; the company headquarters are in Germany; and the software is in accordance with the European Union General Data Protection Regulations (GDPR—sometimes referred to as DSGVO in Germany). The data are directly recorded digitally and do not have to be entered separately by hand, which minimises the risk of input errors.

#### Coding process

Since there will be four measurement time points, the data cannot be collected completely anonymously, but are initially requested pseudo-anonymously. This enables the individual data records to be merged. The complete anonymisation of the data will take place after the 6-month follow-up. A written assignment of code to individual students is completely dispensed with in order to protect data. The data will not be passed on to third parties and the results will not be transmitted by email or post. The ethical and legal aspects according to the declaration of the World Medical Association in the current version will always be observed during data collection and processing.

#### Data security

The data will be transmitted via a secure network of the University of Würzburg. It will be impossible to assign the devices used to the individual adolescents by storing the IP address. The transmission of the data or the recording and storage of the results of the measurements are subject to a tested data protection concept. The digitally collected data will be encrypted at all times. Only authorised members of the study team will have access to the processes of data collection and monitoring of data processing.

#### Data storage

The anonymised data will be electronically stored on the servers of the computer centre of the University of Würzburg, password-protected, and deleted 4 years after the end of the study in accordance with data protection regulations. If a participant revokes his/her declaration of consent to participate in the study, the data obtained up to that point will be excluded from further analysis and destroyed, if they are still available in pseudonymised form. However, if the data have already been anonymised, they can no longer be assigned to the students. Accordingly, the data cannot be deleted. The adolescents and their legal guardians will be provided with detailed information in this regard.

### Confidentiality {27}

All information related to the study and its participants will be stored securely in either locked files or cabinets. Furthermore, information that contains personal identifiers (e.g. names) will be stored separately. Concerning this trial, there will be no list of names assigned to pseudonyms.

### Plans for collection, laboratory evaluation, and storage of biological specimens for genetic or molecular analysis in this trial/future use {33}

Not applicable. There are no plans for the collection of biological specimens and there will not be any genetic or molecular analysis.

## Statistical methods

### Statistical methods for primary and secondary outcomes {20a}

The intervention group will be compared to the waiting list control group in terms of the difference in change. The data structure will be clustered at different levels (school type, school, grade, class, student), and we must take this into account. To check for the impact of levels, the ICC will be calculated. If the ICC is bigger than 0.1, we will analyse the data using (general) multilevel models. If not, mixed ANOVAS will be performed. First, a null model will be built consisting of the dependent variable and the random intercept. The model fit will be given using the Akaike information criterion AIC. Based on the null model, the independent variables of interest will be included, for the primary outcome self-perceived stress (measured with the PSS-10) and for the secondary outcomes the remaining measure (DERS-SF, SCS, ISI, PHQ-4, CD-RISC, SEED, DSHI-6, SISE, WHO-5, protective factors, FAS III). The AIC will be used to compare the models to one another.

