### Sample size {14}

To analyse cluster-randomised trials, specific constraints must be followed, as individuals within a cluster are assumed to be more similar compared to individuals from different clusters. In order to detect significant effects, the sample size of the trial must be adjusted. This so-called clustering effect (1 + (*m*-1)×*p* [*m* = average number of subjects per cluster; *p* = intraclass correlation coefficient (ICC)]) resulted in an estimated *N* = 1795. For *m*, we assumed an average of 80 within an entire grade as the average class size in Germany varies nationwide (21.2–30.4 students per class), and the ICC was estimated quite conservatively at approximately 0.05 [70] on the basis of the primary outcome. Hence, a clustering effect of 4.95 was determined. Assuming a small effect size (Cohens *d* = 0.2) in universal prevention based on previous studies [71], with a significance level alpha = 0.05 and a power = 0.9, g*power suggests a total of *N* = 306 [72]. Considering the clustering effect, we have to multiply this by 4.95, reaching an overall *N* = 1515. Assuming a dropout rate of 25% due to moving out of the area, sickness, or other reasons, we must add another 379, leading to the final *N* = 1894.

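### The confirmatory model for PSS-10 is left to an ICC switch and AIC comparison, and the difference-in-change contrast names no baseline adjustment, which costs some precision (about 3-23% of variance under assumed correlations)

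*Protocol article*

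**What the plan says.** All of this is in the protocol article, Statistical methods for primary and secondary outcomes {20a}, unless noted.

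- **Contrast:** "The intervention group will be compared to the waiting list control group in terms of the difference in change". Baseline PSS-10 is not named as a covariate, although the Participant timeline {13} has every student complete the full battery at baseline.
- **Choice of method:** "If the ICC is bigger than 0.1, we will analyse the data using (general) multilevel models". The alternative is "If not, mixed ANOVAS will be performed". The text does not say at which level this ICC is taken.
- **Model building:** "First, a null model will be built consisting of the dependent variable and the random intercept". Predictors of interest are then added without being listed, and "The AIC will be used to compare the models to one another". No model is designated as the one that carries the primary test.
- **Time point:** Trial design {8} gives stress after 6 months as the primary endpoint. Outcomes {12} gives the 3- and 6-month follow-ups.

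**The concern.** A confirmatory test needs one model fixed before the data are seen. Here the class of model depends on an observed ICC, and the terms in it are open to comparison by AIC. Two analysts following this section could report different primary estimates.

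The second issue is precision. A contrast of changes in effect fixes the slope on baseline at 1. Adjustment lets the data set that slope and, with suitable covariates, gives a smaller variance from information already collected. In a trial randomised by school, precision between schools is the scarce resource, so it matters how baseline is used.

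**Working it through.** **Inputs from Sample size {14}.** The cluster size is given as "For *m*, we assumed an average of 80 within an entire grade", and the ICC as 0.05. The design effect reproduces: 1 + (80 - 1) × 0.05 = 4.95. The section states no correlation over time and no standard deviation of change, so there is no precision figure for the change contrast to reproduce.

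**Assumed inputs.** Call the correlation over time of the true school levels CAC and that of students within schools SAC. I take CAC from 0.6 to 1.0 and SAC from 0.3 to 0.7.

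**Step 1: what drives the variance.** In a school mean, the between-school share is m × ICC / design effect = 4.00 / 4.95 = 81%. The stability of schools therefore matters more than the stability of students.

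**Step 2: correlation of school means over time.**

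R = [m × ICC × CAC + (1 - ICC) × SAC] / [1 + (m - 1) × ICC] = (4.00 × CAC + 0.95 × SAC) / 4.95.

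**Step 3: relative variances.** With the follow-up school mean scaled to 1, change has variance 2(1 - R). Adjustment for student and school-mean baseline, with optimal slopes, has 1 - R². The ratio of adjusted to change is (1 + R)/2, so the saving is (1 - R)/2.

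| CAC | SAC 0.3 | SAC 0.5 | SAC 0.7 |
|---|---|---|---|
| 0.6 | 22.9% | 21.0% | 19.0% |
| 0.7 | 18.8% | 16.9% | 15.0% |
| 0.8 | 14.8% | 12.9% | 11.0% |
| 0.9 | 10.8% | 8.8% | 6.9% |
| 1.0 | 6.7% | 4.8% | 2.9% |

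Top left: R = (2.40 + 0.285) / 4.95 = 0.542, and (1 - 0.542)/2 = 22.9%. Bottom right: R = (4.00 + 0.665) / 4.95 = 0.942, and the saving is 2.9%.

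**Step 4: own baseline only.** Suppose one common slope is used, b = ICC × CAC + (1 - ICC) × SAC. The variance relative to change is then (1 + b² - 2bR) / [2(1 - R)]. At CAC 0.9 and SAC 0.5, b = 0.52 and R = 0.823, which gives about 0.414 / 0.354 = 1.17. For SAC 0.5 the ratio is 0.80, 0.86, 0.97, 1.17 and 1.70 as CAC goes from 0.6 to 1.0 in steps of 0.1. Adjusting for the student's baseline alone can therefore be less precise than change when schools are stable. The school mean has to be in the model too.

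**Step 5: which branch the planning value selects.** The planning ICC of 0.05 lies below the threshold of 0.1. If the observed ICC matches the planning value, mixed ANOVA is used, although the abstract expects mainly multilevel analyses.

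**The case against.** The best defence is that the article is condensed and an unseen analysis plan may fix the model. The wording does not say that raw change scores will be the dependent variable, nor does it exclude baseline PSS-10 from the added predictors. Under randomisation, change and adjustment target the same group difference without bias. This stands in part: the precision point alone would be a preference. But the article does not merely stay silent. It states a contrast, a switch rule and a model-comparison rule, and together these leave the primary test open.

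Four stronger readings are tempting and are not supported.

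- **A saving of 15-35%.** A reader might apply (1 - r)/2 with student-level correlations of 0.7 to 0.3. That is the formula for individual randomisation. This trial randomises schools, and no r is given. Any gain in power worked out from it rests on the same unsupported basis.
- **Change is worse than ignoring baseline.** That needs R below 0.5. In the table's range R is at least 0.542, so change is more precise than the follow-up score alone.
- **AIC inflates the type I error.** AIC retains a single null term when chi-squared on 1 degree of freedom exceeds 2, which has probability 0.157. That is not the error rate of the group test. The text says only that models are compared by AIC, not that the group effect is read from the best-fitting one.
- **The mixed ANOVA is invalid.** If it ignored schools, the two-sided error for a single-time comparison at a design effect of 4.95 would be about 0.38. The article does not say that schools would be ignored, and the same section says clustering must be accounted for.

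**Conclusion.** The point holds as one about an unfixed confirmatory model and forgone precision. The ICC switch is an explicit data-dependent rule. AIC comparison is an open selection rule whose effect on the primary test cannot be determined from the text.

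The loss from using change in place of adjustment for both student and school-mean baseline is about 3-23% of variance. It falls below 15% once the school-level correlation reaches 0.8. The range rests on three things:

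- The correlations are assumed.
- The cluster size of 80 refers to one grade, while schools are randomised and may enter several grades.
- The formula takes the slopes as known. With 1894 / 80, or about 24 clusters, estimating the school-level slope uses part of the gain and could cancel it at the low end.

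The statement that change is unbiased takes baseline answers as unaffected by allocation. The Participant timeline {13} places assessment 14-30 days after randomisation. That bears on change and adjustment alike and does not decide between them.

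**What to change.** Replace the switch and the build-up for the primary outcome with one prespecified mixed model:

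- **Outcome:** PSS-10 at T2 and T3.
- **Fixed effects:** group, time, group-by-time, student baseline PSS-10 and school-mean baseline PSS-10.
- **Random effects:** school, whatever the observed ICC, plus class and student.
- **Primary estimate:** the group contrast at T3 (6 months), in line with Trial design {8}. Outcomes {12}, which gives 3 and 6 months, must be reconciled with this.
- **AIC:** exploratory models only.

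School type and federal state need not be added, since no stratification is stated and each would use further between-school degrees of freedom.

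No new data are needed. The statistical cost is one between-school degree of freedom for the school-mean covariate: from about 22 (24 clusters less 2 arms) to about 21 at the planning cluster size. The number of schools is not yet known, so this should be checked once recruitment is complete.

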**Methods:**

The effectiveness of the short and economical prevention programme *LessStress* will be examined in a cluster-randomised controlled trial (RCT) encompassing 1894 students. At several measurement time points, students from two groups (intervention and control) will be asked about their subjectively perceived stress levels, among other aspects. Due to the clustered nature of the data, mainly multilevel analyses will be performed.

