## Assignment of interventions: allocation

### Sequence generation {16a}

Participating schools will be randomly assigned to one of the two groups using Microsoft Excel. The randomisation will be carried out on the school level following a 1:1 allocation ratio. This enables interference between the IG and WL to be avoided.

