### Methods for additional analyses (e.g. subgroup analyses) {20b}

We plan to split all of the participant data into subgroups for comparisons between males and females, different school types, age categories (younger vs. older determined by school grade), and healthy vs. clinically relevant. Depending on the variables, different methods will be used (*t*-test, Wilcoxon test, chi-squared), but we prefer multilevel modelling to explore associations between intervention effects and student characteristics.

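### The multilevel model depends on an observed ICC above 0.1, twice the ICC the trial plans on, so the expected primary analysis is a mixed ANOVA with no stated allowance for the randomised schools

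*Protocol article*

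**What the plan says.** Schools are the unit of allocation (Sequence generation {16a}): "The randomisation will be carried out on the school level following a 1:1 allocation ratio".

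The sample size section {14} treats clustering as important. On cluster size, "we assumed an average of 80 within an entire grade"; on correlation, "the ICC was estimated quite conservatively at approximately 0.05"; and from these, "Hence, a clustering effect of 4.95 was determined". The unadjusted number is multiplied by that factor.

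The statistical methods section {20a} compares the groups on the difference in change. It lists five levels (school type, school, grade, class, student), says the clustering has to be allowed for, and then sets the rule: "If the ICC is bigger than 0.1, we will analyse the data using (general) multilevel models. If not, mixed ANOVAS will be performed". It does not say at which level this ICC is computed, or which factors the mixed ANOVA contains.

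The abstract states: "Due to the clustered nature of the data, mainly multilevel analyses will be performed".

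**The concern.** The sample size section and the analysis section do not fit together. One treats an ICC of 0.05 as large enough to multiply the sample almost fivefold. The other treats anything up to 0.1 as too small to need a multilevel model. A fixed ICC threshold is also the wrong kind of criterion: variance inflation depends on cluster size as well as ICC, and with about 80 students per cluster even a small ICC matters.

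If the ANOVA branch is taken and school is not in it, students are treated as independent although whole schools were allocated. Standard errors are then too small, and chance differences between schools can be reported as an effect of LessStress on the primary outcome.

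**Working it through.** **Inputs from the protocol.** m = 80, ICC = 0.05, unadjusted N = 306, 25% dropout ({14}); threshold 0.1 and difference in change as target ({20a}); alpha 0.05, with sidedness not stated and two-sided assumed here.

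**Inputs assumed (not in the protocol).** 24 schools for the simulations (1894 / 80 = 23.7; the protocol says the number cannot be predicted); 60 students per school as a second cluster size (80 less 25%); within-student correlation r_e of 0.4 to 0.6; school-effect correlation between waves, r_s, varied.

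**1. The plan's own figure.** Design effect = 1 + (m − 1) × ICC = 1 + 79 × 0.05 = 4.95. Then 306 × 4.95 = 1514.7, rounded to 1515, and 1515 × 1.25 = 1893.75, rounded to 1894. All three figures reproduce.

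**2. Which branch is taken.** The planning value of 0.05 is half the threshold. With 24 schools of 80 and a true ICC of 0.05, the estimated ICC exceeded 0.1 in fewer than 1% of simulated trials. Even at a true ICC of 0.09 it did so in only 31%.

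**3. Follow-up scores, school ignored.** True error = 2 × (1 − Φ(1.96 / √design effect)).

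- ICC 0.05, m = 80: 1.96 / √4.95 = 0.881, giving 0.378.
- ICC 0.01, m = 80: design effect 1.79, 1.96 / √1.79 = 1.465, giving 0.143.
- ICC just under 0.1, m = 80: design effect 8.9, giving 0.511, and still sent to the ANOVA.
- ICC 0.05, m = 25: design effect 2.20, giving 0.186.

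**4. Difference in change, school ignored.** With unit variance at each wave, the ICC of the change score is ICC × (1 − r_s) / [ICC × (1 − r_s) + (1 − ICC) × (1 − r_e)]. For r_s = 0.9 and r_e = 0.6 this is 0.005 / (0.005 + 0.38) = 0.0130. With m = 80 the design effect is 1 + 79 × 0.0130 = 2.03, and the error is 0.168. At ICC 0.05, for m = 60 to 80:

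| School-effect correlation r_s | r_e = 0.4 | r_e = 0.6 |
|---|---|---|
| 1.0 | 5% | 5% |
| 0.95 | 8–9% | 10–11% |
| 0.9 | 11–13% | 14–17% |
| 0.8 | 17–20% | 22–26% |

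Simulation with 24 schools and r_e = 0.6 gave 14–17% at r_s = 0.9 and 23–27% at 0.8, in line with the formula.

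A smaller ICC reduces this. At ICC 0.01, r_s = 0.9, r_e = 0.6 and m = 80, the change-score ICC is 0.001 / (0.001 + 0.396) = 0.0025, the design effect 1.20 and the error about 7%.

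**5. School accounted for.** In the same kind of simulation, a test on school means had an error of about 4.5% to 6%.

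**The case against.** **The ANOVA might include school.** Its terms are not given, so a reader who infers that the plan says it will ignore schools goes further than the text. What stands is that it is offered as the alternative to multilevel models, that the usual between-within ANOVA has no school term, and that nothing in the article supplies one.

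**The ICC level is open.** If the ICC were computed for classes, or for repeated measures within students, it could exceed 0.1 and lead to the multilevel branch. That ambiguity is real. The only definition in the article, in {14}, concerns subjects within a cluster.

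**Change scores remove stable school differences.** This is correct, and the error is 5% if school effects are identical at both waves. The 38% therefore should not be read as the false-positive rate of the stated analysis of change. It applies to a comparison of follow-up scores, which is how the outcomes section {12} words the primary outcome (group differences at 3 and 6 months). Nothing in the article supports perfect stability over six months.

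**The abstract.** It speaks of mainly multilevel analyses, which allows exceptions, so it is not a flat contradiction. The firm conflict is between {14} and {20a}.

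**Subgroups.** A reader might infer from {20b} ("different methods will be used (*t*-test, Wilcoxon test, chi-squared") that the intervention effect will be tested in subgroups without regard to clustering. The same sentence goes on to prefer multilevel modelling for associations between intervention effects and student characteristics. The simple tests are described as comparisons of sexes, school types and age groups, not as tests of the intervention, and the factor 4.95 does not carry over to comparing boys with girls.

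**Conclusion.** The rule in {20a} is wrong as written and should be changed before analysis. Its threshold is twice the planning ICC, so on the plan's own assumption a school-randomised trial goes to an analysis with no stated allowance for school, and no other section repairs this.

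The size depends on what is tested. For change, the inflation ranges from small to about five times nominal over the conditions tabulated, and vanishes only if school effects are perfectly stable. For follow-up scores it is large even at ICC 0.01. The change figures rest on correlations the protocol does not give, so they are a range and not a prediction. The sample size section takes a grade as the cluster although schools are randomised; if a school contributes several grades, clusters are larger and the inflation greater.

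**What to change.** In {20a}, delete the ICC threshold and the mixed-ANOVA branch. State that every between-group comparison, primary and secondary, accounts for the randomised school whatever the observed ICC. This can be a multilevel model with a random school effect (plus school-by-time if waves are modelled jointly) and small-sample degrees of freedom such as Kenward-Roger or Satterthwaite, or an equivalent cluster-level analysis. The ICC can still be reported, with its level named, but should not select the model.

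In {20b}, make the multilevel model that is already preferred the rule for any subgroup test of the intervention effect.

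The cost is a few sentences. Confidence intervals will be wider but valid, and the sample size already carries an inflation factor meant for such an analysis.
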